#### Process evaluation

The evaluation is based on the Medical Research Council (MRC) as the core framework^32^ and is complemented with the normalisation process theory (NPT).^33^ The MRC framework explores the contextual factors that interact and influence during the implementation of the intervention.^34^ We will focus on (1) monitoring the intervention delivery and (2) the reception of the intervention, in terms of the following subcomponents: reach, dose (delivered and received), fidelity and acceptability.^34^ NPT is a theory that explains the social processes when implementing complex behavioural interventions in the healthcare practice.^33^ The four constructs (coherence, cognitive participation, collective action and reflexive monitoring) will be assessed in the people who have received some components of the intervention and can be examined using the Normalization Process Theory Questionnaire (NoMAD tool).^35^ The process evaluation will encompass a mixed-method approach using surveys, observations, checklists and interviews with different actors.

Figure 1 shows the different evaluations, moments and tools to be used.

**Figure 1 F1:**
[figure not shown]
Graphical representation of the implementation of COmmunity HEalth System InnovatiON Implementation (COHESION-I) project. ^1^The implementation of the communication strategy is integrated within the quantitative and process evaluation. The process evaluation has three types of evaluation: Mechanism of impact, Context and Implementation outcomes (1 = community, 2 = healthcare workers and 3 = health facility). *Field workers will participate at moment 5 by making field notes on the project context. WHO RST, World Health Organization Responsiveness; EQ-5D-5L, EuroQol 5 dimensions 5 levels; FCHV, female community health volunteers; HCW, healthcare worker; NTD, neglected tropical disease; PHC, primary healthcare; PSQ-18, Patient Satisfaction Questionnaire Short Form; PVS, People’s Voice Survey; HTP, hypertension; DB, diabetes; Tx, access to treatment and medication; QK, Questionnaire of knowledge; QLH, Questionnaire on lifestyle habits.

### Participants and selection criteria

Table 1 details the general characteristics of participants across the three countries and the criteria used for the selection of participants. The COHESION-I project involves seven types of key actors at the macro, meso and micro levels of the health system that will participate in each type of evaluation. These participants will be recruited in all arms.

**Table 1 T1:** Participants and inclusion criteria

Component	Level	Type of participant	Inclusion criteria
Quantitative evaluation	Micro	PHC users	18 years of age or older. Live in one of the selected rural, peri-urban or urban sites in the three countries.
		PHC users with chronic conditions	18 years of age or older. Live in one of the selected rural or suburban sites in the three countries. Have a diagnosis of diabetes or hypertension or selected NTD in each country. To complement the levels of low awareness, measurements will be taken in those 30 years of age or older (initial survey). The criteria are: having blood pressure (≥140 mm Hg systolic, or ≥90 mm Hg diastolic, average of two readings) and/or having a high risk of diabetes by FINDRISC and a fasting glucose test.
Qualitative evaluation	Micro	PHC users with chronic conditions	18 years of age or older. Live in one of the selected rural or suburban sites in the three countries. Have an established diagnosis of the disease for at least 2 years at the time of the first interview. Be health services users (female or male) with chronic conditions. Have used the local PHC services in the last 12 months.
		Healthcare workers*	Be a healthcare worker who provides the health services in the local PHC facilities in the three countries. Be involved in the non-communicable and/or neglected tropical diseases department (not exclusive).
Economic evaluation	Micro	PHC users with chronic conditions	Same inclusion criteria of the quantitative evaluation.
Process evaluation	Macro	Decision makers from national government*	Have a role in the national state of the three countries during the period of the interviews. Have a role in the non-communicable and/or neglected tropical diseases department (not exclusive).
	Meso	Decision makers from regional/state/local government*	Have a role in the regional state of the three countries during the period of the interviews.
	Micro	PHC users with chronic conditions	Be health service users with chronic conditions. Have used the health services in the previous 3 months.
		Not PHC users	18 years of age or older. Not be health service users or people who have not used PHC services for at least 12 months.
		Healthcare workers	Be a healthcare worker who provides the health services in the local PHC facilities in the three countries.
		Community healthcare workers†	Female community healthcare volunteers and members of the health committees. Have participated in the training of the intervention.
		Local authorities	Be a local authority in one of the selected rural or suburban sites in the three countries. Be a local authority during the period of the interviews and have knowledge about the situation of their community.

* Ideally, participants will be the same in the different measurements.

† Only for Nepal and Mozambique.

FINDRISC, The Finnish Diabetes Risk Score; NTD, neglected tropical disease; PHC, primary healthcare.

To complement the low awareness in Peru regarding blood pressure levels and diabetes diagnosis, the quantitative and economic evaluation will conduct a two-step diabetes screening. In order to conduct the diabetes screening, the Finish Diabetes Risk Score (FINDRISC) will be used and a fasting glucose in those identified at high risk in the countries will be measured.^36^ In the three countries, to recruit participants for the qualitative study, the research team will contact local leaders from sites and health promoters and, after explaining the aim of the COHESION-I project and the study, they will be asked for references of community members meeting the selection criteria for this study. Recruitment strategies will aim to have a similar number of women and men participating in the study.

### Intervention

The intervention in the three countries was decided using co-creation as it was described in previous studies^14 37^ and it will be delivered after approximately 6 months from the initial survey. The intervention will last 7 months.

During the co-creation process, different stakeholders participated in defining its components in the COHESION project. Each of these components was aimed at promoting change at the community level, among healthcare workers and within health facilities. Specific details of each component will be decided during the co-design process. However, some key aspects are already decided, and the Template for Intervention Description and Replication (TIDIeR) checklist^38^ is used to share this information (table 2).

**Table 2 T2:** Intervention description using Template for Intervention Description and Replication (TIDIeR)

	Peru	Mozambique	Nepal
*Why and what*	During the formative studies and co-creation process, it was decided to include: **Radio programmes, spots or podcasts** to motivate service users to clarify concerns about their health condition and treatment. For healthcare workers, ***c*apacity building on management of diabetes, hypertension and NCC, as well as clear communication** will be included. The training will provide a set of skills that are lacking between healthcare workers. **A communication tool** will be developed to use during consultation to promote more interaction between healthcare workers and service users. The intervention will also include **a component related to decentralised decision-making to enhance PHC facilities**. This component will consist of a small grant for the community to decide how to spend the money to improve the equipment and/or infrastructure of the health facility.	Similar to Peru, it was decided to include **a communication strategy** as well as **capacity building for healthcare workers**. However, the communication strategy will use other channels such as videos through PHC TV. Likewise, an ‘**information booth’** will be established to use in the health facility to improve the communication between healthcare workers and user services. This booth enables healthcare workers to be better informed and offers clear information to service users. In addition, **group discussions will be performed between healthcare workers to express their challenges and opportunities during the consultation**, in order to have a better comprehension of each user, identify needs and issues more efficiently. Regarding the health facility, it will include a component related to the **improvement of the appointment system (similar to the one available for HIV) and the advocacy on the issue of access to medicines**. This component aims to improve the quality of basic needs in the health facility.	Similar to Peru, it was decided to include **a communication strategy,** as well as **capacity building for healthcare workers**. In addition, this component will include the **participation of female community health volunteers**. Also, a **flip chart and guidelines** for management of diabetes and hypertension will be created and also will be part of the training for healthcare workers to provide the guide and confidence to attend to the needs of patients in the consultation. **The health facility component will adopt a similar approach to that in Peru**. It will consist of **posters on diabetes and hypertension, supplemented by questions to have a better understanding of health conditions** and improve communication between health staff and service users.
Who provided	The radio programmes, spots or podcasts content will be created with input of people with different expertise such as NCDs, NTDs, local authorities, service users, healthcare workers and experts in behavioural sciences and communication. The training content for healthcare workers will be developed and delivered by experts in PHC and medical education as well as local trainers. The communication tool will be used by the healthcare workers, and they will be trained by the research team.	The communication component, as well as the training for healthcare workers, will follow a similar approach to Peru. The ‘information booth’ and group discussions will be implemented in the health facilities and will be conducted by healthcare workers. The appointment system and the medication equity promotion will be structured by the research team, healthcare workers of health facilities, experts in PHC and local authorities.	The communication component will be developed by a diverse group of experts, reflecting a similar approach to Peru and Mozambique. Similarly, the training structure for the healthcare workers component will be crafted by seasoned professionals in PHC and medical education, complemented by the cultural insights of local trainers. On the other hand, collaboration among healthcare workers, the research team, and community stakeholders will inform the development of the facility component, which entails implementing posters addressing clinical conditions.
How	The radio programmes, spots or podcasts will be delivered through the local community radio/loudspeaker or social media (WhatsApp or Facebook) to disseminate the information. The training for healthcare workers will be provided face-to-face with some additional resources and information delivered through videos and/or documents. The communication tool will be printed, and the cards will be available in each healthcare worker consultation of the health facilities. The facility grant will be provided by the research team according to a predefined budget.	The communication component will also be delivered through TV or social media (Facebook and WhatsApp) to disseminate the information. The training will be imparted principally face-to-face and complemented with media resources. The material for the ‘information booth’ will be printed and produced to be available at the health facilities. Similarly, material for the promotion of access to medication will be developed and made available at each centre.	The community component will be disseminated via radio or loudspeaker systems, or through social media platforms (Facebook) as observed in other countries. Healthcare worker training will be conducted in person and complemented with supplementary resources. Flip charts and guidelines will be developed and printed for availability to healthcare workers during consultations. Additionally, concerning the health facility component, the poster materials will be printed and strategically placed within the health facility to assist healthcare workers.
Where	The intervention occurred within the PHC level, most of the activities are in the health facility but some of them could be part of the home visits.		
When and how much	Many of these characteristics will be defined in the co-design process.		
Tailoring	The intervention is tailored to the needs and expectations of the local contexts as a result of the ongoing co-design process. However, due to the diversity of community members, the research team cannot ensure the co-designed tools will fit everybody.		

NCC, neurocysticercosis; NTD, neglected tropical disease; PHC, primary healthcare; TV, television.

### Outcome

The primary and the secondary outcomes for each component are detailed in table 3 and online supplemental tables 2, 3.

**Table 3 T3:** Outcomes

Evaluation type	Outcome level	Representative outcomes	Measurement instruments/data sources	Collected from	Time
Quantitative evaluation	Primary outcomes	Patient satisfaction; health system responsiveness; People’s Voice Survey; quality of life	PSQ-18; WHO responsiveness tool; People’s Voice Survey; EQ-5D-5L	PHC users with chronic conditions (HTP, DB, NTD); PHC users	Initial survey; M2–M5
	Secondary outcomes	Access to care and treatment for HTP and DB; disease control (blood pressure, glycaemia); health literacy and behaviours (diet, service use)	Self-reported surveys; blood pressure and glucometer measurements	PHC users with chronic conditions (HTP, DB, NTD); PHC users	Initial survey; M2–M5
Qualitative evaluations	Primary outcomes	Perceived value of care; patient satisfaction; roles and responsibilities; perceived capacity	In-depth interviews; interviews	PHC users with chronic conditions (HTP, DB, NTD); HCWs	Initial survey or M1, M3, M5
Economic evaluation	Primary outcomes	Cost of services provided; out-of-pocket expenses; cost per QALY gained; cost per satisfied patient; cost per responsive patient	Facility-level cost questionnaire; household out-of-pocket questionnaire; costs calculated previously	PHC users with chronic conditions (HTP, DB, NTD); PHC users	M1, M5
Process evaluation	Context	*Barriers and facilitators:* environmental context during COHESION-I implementation; community and regional support; influences on intervention; team dynamics	Fields notes; meso-level and local leader questionnaires; Team Climate Inventory	Field workers; decision-makers; community members; PHC users with chronic conditions; non PHC users; HCWs	M1, M5
		*Health system-level indicators:* service delivery and workforce performance; access and affordability of care; patient empowerment; community engagement	Semi-structured interviews; service evaluation checklists; facility and stock records; brief provider and patient surveys	Community members; PHC users with chronic conditions; HCWs	M1 - M5
	Implementation outcomes	Online supplemental table 3*			
	Mechanism of impact	Coherence; cognitive participation; collective action; reflexive monitoring (NPT constructs)	Semi-structured interviews using NPT framework	PHC users, community members, HCWs; decision-makers; local authorities	M1 – M5 (variable, see online supplemental table 2)
Communication strategy†	Quantitative evaluation perspective	Comprehension of chronic disease concepts; risk awareness; preventive health behaviours	Questionnaire of knowledge; questionnaire on lifestyle habits	PHC users; PHC users with chronic conditions (HTP and DB)	M1, M5
	Process evaluation perspective	Exposure to themes of communication strategy; remembrance and comprehension of communication messages on chronic diseases	Semi-structured interviews	PHC users with chronic conditions (HTP and DB)	M3

* For the implementation outcome from the process evaluation, the online supplemental table 3 was developed.

† The evaluation of the communication strategy will be integrated into the quantitative and process evaluation.

COHESION-I, COmmunity HEalth System InnovatiON Implementation; DB, diabetes; EQ-5D-5L, EuroQol 5 dimensions 5 levels; HCWs, healthcare workers; HTP, hypertension; M, Moment; NPT, normalisation process theory; NTD, neglected tropical diseases; PHC user, user who received care in one of the primary healthcare facilities; PSQ-18, Patient Satisfaction Questionnaire Short Form; QALY, quality-adjusted life-years.

#### Sample size for the qualitative and process evaluation

##### PHC users (n=8 interviewees/arm): qualitative evaluation

In each of the three arms, eight people will be interviewed. A total of 24 interviews per country will be conducted per data collection moment. Out of the 24 participants, 12 should be between 30 and 45 years old, and the rest above 45 years old. In each arm, we will aim to have at least two males and two females with HTP, two females with the selected NTD, and two males and two females with diabetes. The same participants will be interviewed at the three moments of time previously mentioned. This will enable understanding of how their expectations and experiences change *through time* as the intervention is being implemented.

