#### Qualitative evaluation

The qualitative evaluation will include two studies: a qualitative longitudinal study with local PHC users and a qualitative study with healthcare workers. The qualitative evaluation will be guided by the ‘lay evaluation of healthcare’ theoretical framework proposed by Calnan,^25^ value theory^26^,^29^ and the WHO responsiveness framework.^30^

The longitudinal qualitative study aims to explore the experiences of adult women and men living with diabetes, hypertension or the specific neglected tropical disease and how they unfold *through time*^31^. The data will be collected at different moments (initial survey, moments 3 and 5) with the same participants through in-depth and semi-structured interviews. Photo-elicitation will be used, if participants accept, to evoke conversations during the interviews.

The qualitative study with healthcare workers will examine *over time* the perceived roles and responsibilities of healthcare workers in providing care for PHC users with chronic conditions. The interviews will be conducted at three different moments, before, during and after the intervention implementation.

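### The interview targets for the longitudinal qualitative study do not match its stated population, sex balance or own total: women only for the NTD, nobody under 30, and cells summing to 10 per arm against 8

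*Protocol article*

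**What the plan says.** Four places in the protocol article bear on who is interviewed in the longitudinal qualitative study of service users.

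- **Study design, Qualitative evaluation.** The aim is to "explore the experiences of adult women and men living with diabetes, hypertension or the specific neglected tropical disease".
- **Participants and selection criteria, Table 1, qualitative row.** The entry begins "18 years of age or older. Live in one of the selected rural or suburban sites in the three countries", and sex is open: "Be health services users (female or male) with chronic conditions".
- **Participants and selection criteria, text after Table 1.** Directly after describing recruitment for the qualitative study, it says: "Recruitment strategies will aim to have a similar number of women and men participating in the study".
- **Sample size for the qualitative and process evaluation, PHC users.** "In each of the three arms, eight people will be interviewed", and "A total of 24 interviews per country will be conducted per data collection moment". On age, of the 24, "12 should be between 30 and 45 years old, and the rest above 45 years old". The minimum targets per arm are two men and two women with hypertension, two men and two women with diabetes, and, for the NTD, "two females with the selected NTD". The same people are followed through all three interview rounds.

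No reason is given for the women-only NTD target or for starting the age bands at 30.

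**The concern.** The aim, the eligibility criteria and the recruitment statement describe adults of both sexes from age 18. The sampling targets are narrower on sex for one of the three tracer conditions, and narrower on age for all of them. They also do not add up to the number of interviews planned.

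What is at stake is the reach of the findings. The Qualitative analysis section says intersectional-gender and sociocultural dimensions will be considered. If the NTD accounts come only from women, gender cannot be examined within that group, and any difference between NTD accounts and diabetes or hypertension accounts is mixed with a difference between women and men. The write-up could then describe adult women and men with these conditions although part of that population had no planned place. Because the panel is fixed, a group missed at the first round is not added later.

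**Working it through.** This is a quota sample, so the check is a count. All inputs are from the PHC users subsection on sample size unless stated.

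**1. Stated total.** 3 arms × 8 = 24 per country per round. This reproduces.

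**2. Age bands.** 12 aged 30–45, and the rest, 24 − 12 = 12, above 45. Places left for ages 18–29: 24 − 12 − 12 = 0. Table 1 admits this group.

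**3. Condition-by-sex cells per arm.**

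| Condition | Men | Women |
|---|---|---|
| Hypertension | 2 | 2 |
| Diabetes | 2 | 2 |
| NTD | 0 | 2 |
| Sum | 4 | 6 |

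The cells total 4 + 6 = 10 per arm and 10 × 3 = 30 per country, so the stated 8 and 24 do not reproduce. The excess is 2 per arm and 6 per country. Women hold 6/10 = 60% of the cells.

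**4. NTD places reserved.** Women: 2 × 3 arms = 6 per country, and 6 × 3 = 18 over three countries. Men: 0 at every level.

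**5. Can the cells fit into 8?** Only if some people count in more than one cell, which the protocol does not say. Take *d* as the number per arm with both hypertension and diabetes, each filling two cells. People needed = 10 − *d*.

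| *d* | People needed | Spare places of 8 |
|---|---|---|
| 0 | 10 | −2 |
| 1 | 9 | −1 |
| 2 | 8 | 0 |
| 3 | 7 | 1 |
| 4 | 6 | 2 |

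The cells fit from *d* = 2. A place that could go to a man with the NTD appears only from *d* = 3. This counts hypertension–diabetes overlap only; a participant with the NTD and one of the other conditions would also change the count.

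**6. Sex split once the cells fit.** The 6-to-4 split belongs to a total of 10, which the plan does not have. At *d* = 2 the split depends on who has both conditions:

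- two women: 6 − 2 = 4 women and 4 men;
- one of each: 5 women and 3 men;
- two men: 6 women and 4 − 2 = 2 men.

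The targets therefore do not secure similar numbers by sex, although one combination reaches it.

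**7. Size of two simple repairs.** Adding two men with the NTD per arm gives 12 per arm, 36 per country and 36 × 3 = 108 interviews over three rounds, against 24 × 3 = 72 planned. Replacing the two NTD women by one woman and one man leaves the cells at 10, so that change alone does not cure the mismatch with 8.

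**The case against.** A reader might infer that men with the NTD and adults under 30 are excluded and go unheard in the project. The documents do not support that.

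- The cells are worded as aims and minimums. Nothing bars a man with the NTD, and 18 women to 0 men describes reserved places, not the achieved sample.
- The process evaluation interviews 12–18 users per arm, with and without chronic conditions, and deliberately across age groups. The quantitative evaluation admits adults from 18 with the NTD and plans 40% men. Both can reach these groups.

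A reader might also infer that condition is confounded with sex in a way that biases a result. That is also too strong. Hypertension and diabetes each have equal targets for men and women, so the mixing concerns only the NTD against those two. The qualitative objective concerns how users' and healthcare workers' perceptions differ and change, and the analysis is interpretative with cross-country comparison. No qualitative contrast between the NTD and the other conditions is planned; analysis by condition appears only under Secondary endpoint analysis. The aim joins the conditions with 'or', so it does not promise both sexes within each, and the recruitment statement on sex is about overall numbers.

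Finally, quotas narrower than eligibility are ordinary in purposive sampling.

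These points limit the consequence but do not remove the mismatch. The narrowing is unexplained, and the age bands, unlike the cells, carry no minimum wording and use every place. The 30-year threshold in Table 1 belongs to measurements in the initial survey, and the two-year diagnosis requirement in the qualitative row is not given as a reason for the bands. The minimum wording gives little room, because the cells already exceed the places.

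**Conclusion.** The point holds as a minor internal inconsistency. The NTD target reserves two places per arm for women and none for men. The cells sum to 10 per arm (30 per country) against a stated 8 (24) and run 6 women to 4 men. The age bands leave 0 of 24 places for eligible adults aged 18–29.

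Men with the NTD are not formally barred. Within 8 per arm a place opens for one only if at least three people have both hypertension and diabetes, assuming that is the only overlap counted and all targets are met.

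The consequence is confined to the longitudinal interviews: it restricts what can be said about gender within the NTD group, about NTD against other accounts, and about adults under 30. It biases no effect estimate. Who was actually recruited is not in the document.

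**What to change.** **Where recruitment is still open.** Restate the per-arm cells so that they sum to 8, or state that a person with both hypertension and diabetes counts in both cells. Include both sexes for the NTD, with similar numbers of women and men overall. Make the age bands and the Table 1 minimum age agree, either by starting the lower band at 18 or by setting the minimum for this study at 30.

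**Where the panel is already fixed.** This may be all three countries: Table 3 puts first interviews at the initial survey or Moment 1, and Project status has Peru at Moment 3, Nepal at Moment 2 and Mozambique starting Moment 2 in December 2025. In that case, report the achieved mix of sex, age and condition. If no men with the NTD or no adults under 30 were recruited, limit the stated scope to women for the NTD and to adults aged 30 or over, respectively.

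**Cost.** Either route is a change of wording and needs no extra interviews if 8 per arm is kept. The price is fewer participants per cell, so that one dropout could empty a cell, or a narrower stated scope.
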